### Data collection timepoints

The following measures will be collected online via a secure data system at three time points: Time 1 = 0 weeks (before randomisation to trial conditions), Time 2 = at the end of week 10 (immediately after the intervention group has completed the intervention), and Time 3 = 3 months after the intervention group has completed the intervention and immediately after the control group has completed the intervention. Each questionnaire takes about 10–15 min to complete. To thank participants for their time, after completing the third questionnaire they will be able to download a tailored package of resources about early childhood and development produced by the PRC.

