### Trial outcomes

The primary outcomes of the trial are educator confidence and skills in working with parents, and parent satisfaction with interactions with their child’s educator. Secondary outcomes include parent inclusiveness at centre, supportiveness of centre, parenting involvement with their child’s centre and learning, staff satisfaction with using *Partnering with Parents*, parent satisfaction with discussing concerns with educators, and parent psychological distress (parenting competence and confidence, parenting stress). We expect there will be greater change from Time 1 to Time 2 for the intervention group than for the control group and we expect that the change will be maintained or further improved at three-month follow-up (Time 3).

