### Modelling strategy

Our approach to model choice is based on four main criteria: the characteristics of the data, model pre-specification informed by the previous literature, diagnostic plots and assessment of model appropriateness. We will undertake exploratory analyses of the following possible interactions to assess whether the effect of the *Partnering with Parents* practice support system intervention is modified by factors such as the experience of carers, or number of children under the educators’ care. These analyses will inform the choice of moderators for the analysis described below. An a priori model-fitting analysis strategy will also be developed to identify the order in which covariates and moderator effects are to be included in the model. We will treat services and individuals as random effects to account for the correlation of outcomes for individuals that belong to the same cluster (within cluster correlation) [25], and repeated measures of the same individual over time (within-individual correlation).

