### Analysis of primary and secondary outcome measures

An intention-to-treat multi-level analysis will be conducted for each of the outcome measures with level 1 data reflecting each assessment period, level 2 data reflecting individual participants and level 3 data reflecting the various services. Changes in the outcome measures will be compared for the intervention and control groups assuming appropriate distributions for the outcome measures. Random intercepts will be assumed, while allowing for the clustered nature of the data, and adjusting for appropriate covariates as fixed effects. The model will include an indicator variable for the study groups (0 = control, 1 = intervention) as a fixed effect at level 3 and an integer time variable (1 = baseline, 2 = time2 and 3 = time3) as a random effect at level 1.

We will report the estimated intervention effect as mean outcome difference for continuous outcomes and odds ratio for binary outcomes between intervention and control groups with 95% confidence intervals and *p*-values [25]. The effect of individual moderators will be incorporated using interaction terms between time, allocated group and the individual moderators [26].

Finally, a completer analysis will be conducted with a repeated measures MANOVA analysis using inverse probability weights to adjust for any attrition bias [27]. This analysis will also account for the correlation between measures from the same participant, while allowing for the clustered trial design.

Furthermore, we will examine responses of the control group before and after receiving the intervention.

As an indication of family-centredness, we will look at items that both educators and parents completed, to compare their perceptions (e.g. whether they both agree the service is a welcoming environment for parents).

All qualitative data (open text questions) will be summarised and examined for themes. Thematic analysis is a multi-stage process involving familiarisation with the data, coding (identifying important features relevant to the research questions), searching for and reviewing themes, and defining and naming them [28].

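### The outcome model treats the pre-randomisation Time 1 score as an outcome with arm means free to differ and compares changes, which is valid but less precise than a model with a common baseline

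*Protocol article*

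**What the plan says.** The model is set out in the protocol article under Analysis of primary and secondary outcome measures. The three levels are "level 1 data reflecting each assessment period, level 2 data reflecting individual participants and level 3 data reflecting the various services". Time enters as "an integer time variable (1 = baseline, 2 = time2 and 3 = time3) as a random effect at level 1", so Time 1 is one of the modelled occasions. For the arms, "The model will include an indicator variable for the study groups (0 = control, 1 = intervention) as a fixed effect at level 3". The comparison is described as "Changes in the outcome measures will be compared for the intervention and control groups assuming appropriate distributions for the outcome measures". Covariates are left general: "adjusting for appropriate covariates as fixed effects". Modelling strategy adds the random effects: "We will treat services and individuals as random effects to account for the correlation of outcomes for individuals that belong to the same cluster".

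Trial outcomes frames the hypothesis in the same way: "We expect there will be greater change from Time 1 to Time 2 for the intervention group than for the control group". Data collection timepoints places the first questionnaire at "Time 1 = 0 weeks (before randomisation to trial conditions". The sections on consent and on randomisation agree with that order. Participants shows that everyone entered the trial by completing Time 1 (118 educators, 302 parents).

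Nowhere does the article impose a common Time 1 mean or name the Time 1 score as a covariate.

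**The concern.** Allocation cannot have affected Time 1, so the true difference between arms there is zero in expectation. A model that leaves the arms free at Time 1 estimates that difference and subtracts it, so the estimated effect carries the full noise of the baseline score. A model that uses the known equality does not.

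Precision is scarce here, above all for educators, whose confidence and skills form a primary outcome. There are 16 services in matched pairs plus one group of three rural services, hence 17 randomised units. With 118/17 = 6.9 educators per unit, and borrowing for educators the two ICCs that Power analysis gives for parents, the design effects are 1 + 5.94 × 0.03 = 1.18 and 1 + 5.94 × 0.06 = 1.36. The effective numbers are about 118/1.18 = 100 and 118/1.36 = 87 before any attrition, below the 102 that Power analysis requires. Time 2 is also the only follow-up at which the controls have not yet had the intervention.

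**Working it through.** **The plan's own figure.** Power analysis gives a required effective sample of 102 for d = 0.5, 5% significance and 80% power. A one-sided two-sample t-test reproduces it (51 per arm); a two-sided test needs about 128. That mismatch with the two-sided rule under Baseline analysis is a separate point. What matters here is that 102 is the figure for a plain two-group comparison, so it neither shows nor rules out a gain from baseline. The article gives no Time 1 to Time 2 correlation, so a range is assumed.

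**Inputs.** Services: 19. Average per service: 302/19 ≈ 16 parents and 118/19 ≈ 6 educators. ICC: 0.03 and 0.06 (Power analysis, stated for parents, applied here to both groups). Assumed: correlation r between Time 1 and Time 2 within a person, cluster autocorrelation c of 1 (stable service effects, as random intercepts imply) or 0.8, equal service sizes, complete data, continuous scale. Time is taken as categorical, because the hypothesis concerns the Time 1 to Time 2 change.

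**Step 1, ignoring clustering.** In common units, the variance of a difference in changes is 2(1 − r), and of a baseline-adjusted difference 1 − r². The proportion saved is 1 − (1 − r²)/[2(1 − r)] = (1 − r)/2, which is 25% at r = 0.5 and 15% at r = 0.7.

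**Step 2, with clustering.** The arms are compared through service means, so r is replaced by R, the correlation between a service's Time 1 and Time 2 means. With m people per service:

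- variance of a service mean: v = ICC + (1 − ICC)/m
- covariance of the two means: w = c·ICC + (r − c·ICC)/m
- R = w/v, and the saving is (1 − R)/2

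The ends of the range are:

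- Parents, largest (ICC 0.03, c = 0.8, r = 0.5): v = 0.03 + 0.97/16 = 0.0906; w = 0.024 + 0.476/16 = 0.0538; R = 0.593; saving 20%.
- Parents, smallest (ICC 0.06, c = 1, r = 0.7): v = 0.06 + 0.94/16 = 0.1188; w = 0.06 + 0.64/16 = 0.1000; R = 0.842; saving 8%.
- Educators, largest (ICC 0.03, c = 0.8, r = 0.5): v = 0.03 + 0.97/6 = 0.1917; w = 0.024 + 0.476/6 = 0.1033; R = 0.539; saving 23%.
- Educators, smallest (ICC 0.06, c = 1, r = 0.7): v = 0.06 + 0.94/6 = 0.2167; w = 0.06 + 0.64/6 = 0.1667; R = 0.769; saving 12%.

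A generalised least squares calculation of the full three-occasion model (9 v 9 services) gives the same percentages:

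| ICC, c | Parents r = 0.3 | r = 0.5 | r = 0.7 | Educators r = 0.3 | r = 0.5 | r = 0.7 |
|---|---|---|---|---|---|---|
| 0.03, 1 | 24% | 17% | 10% | 30% | 22% | 13% |
| 0.03, 0.8 | 27% | 20% | 13% | 32% | 23% | 14% |
| 0.06, 1 | 18% | 13% | 8% | 27% | 19% | 12% |
| 0.06, 0.8 | 23% | 18% | 13% | 29% | 22% | 14% |

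At r = 0.9 the saving falls to 3–7% for parents and 4–6% for educators. With 33% lost at both follow-ups, the parent saving is 10–16% at r = 0.5 and 6–10% at r = 0.7.

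**Step 3, what that means.** For r from 0.5 to 0.7, the confidence interval for the Time 2 effect shortens by 1 − √(1 − 0.079) = 4% to 1 − √(1 − 0.203) = 11% for parents, and by 1 − √(1 − 0.115) = 6% to 1 − √(1 − 0.230) = 12% for educators.

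**The case against.** A repeated-measures model with baseline as the first occasion is standard. It is unbiased under randomisation, and the shortfall in precision does not affect its type I error or coverage. On this view, preferring a common baseline is a matter of taste, and the open covariate wording, together with the a priori fitting strategy promised under Modelling strategy, leaves room for it. The first part stands: nothing here is invalid. The second does not. Time 1 is already fixed as a modelled occasion, and a score cannot sensibly be an outcome and a covariate in the same model. The article has therefore made a choice, and a more precise one is available from the same data.

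The objection also rightly limits the size. Stable service effects cancel in a change, so the unclustered 15–25% overstates the gain, and for that reason it should not be turned into a number of participants lost.

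Two stronger readings are tempting. One is that change scores over-correct for chance imbalance and so bias the trial. That is a statement conditional on an observed imbalance; averaged over randomisations the estimator is unbiased, and services were matched on location, size and quality rating to limit imbalance. The other is that the effect will be read from the group main effect averaged over all three occasions, because no group-by-time term is named outside the moderator sentence. With complete data and equal correlations, that would turn a true 0.5 at Times 2 and 3 into 0.5 × 2/3 = 0.33. But the stated comparison of changes implies an interaction, so the text does not support this reading, though it would be better to rule it out.

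**Conclusion.** The point holds as a loss of precision, not as an error of validity. For continuous outcomes, the planned comparison forgoes about 8–20% of the variance of the Time 2 effect for parents and 12–23% for educators. These figures assume r of 0.5–0.7, ICC of 0.03–0.06, cluster autocorrelation of 0.8–1, equal service sizes and complete data. None of the correlations over time comes from the article. The percentages do not carry over to outcomes reported as odds ratios. The change is worth making because precision is limited and the constraint is guaranteed by design; the trial's conclusions do not become unsafe without it.

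**What to change.** Keep the three-level model with its service and individual random effects. Replace integer time with categorical time, constrain both arms to one common Time 1 mean (no group term at Time 1), and include explicit group-by-Time 2 and group-by-Time 3 terms. Name the group-by-Time 2 term as the intervention effect. Describe the Time 3 term separately: Data collection timepoints says that the controls have completed the intervention by then, so it is not a contrast with untreated services.

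An acceptable alternative is to model Times 2 and 3 only, with the individual Time 1 score as covariate. Adding the service-mean Time 1 score is not free: it uses a service-level degree of freedom with only 17 to 19 units.

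The main fix costs a change of wording and needs no data or recruitment. By the article's own account, Time 2 data were still being collated, no dataset had been analysed and analysts are to be blind to allocation, so the change could be recorded before any comparison of arms.

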**Results:**

One hundred eighteen educators and 302 parents recruited from 19 participating ECEC services have consented to take part in the trial.

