### Baseline analysis (time 1)

As a check for appropriate balance between the control and intervention groups and to provide an overview of the study population [24], both at service and individual levels, data for the control and intervention groups will be compared at baseline. We will present the mean, standard deviation and range for continuous, approximately symmetric variables; medians, interquartile range and range for continuous, skewed variables of clusters. We will describe categorical data with percentages across sub-groups.

All statistical tests and confidence intervals will be two-sided. Between-group comparisons will be presented with 95% confidence intervals and the statistical significance level set will be at the 5% level. In addition, we will account for the clustered nature of the data for all comparative analyses to ensure correct confidence intervals and type I error rates are calculated. In addition, the intra-cluster correlation coefficient for each outcome, based on the adjusted analyses with 95% confidence interval, will be reported.

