### Power analysis

The number of parents recruited for this study is 302. However, the effective sample size is less than this because we have intra cluster correlation (ICC), the value of which is unknown. The required effective sample size to detect a moderate effect size (d = 0.5) with 5% significance and 80% power is 102, which suggests that the sample size recruited is adequate as long as attrition rates are less than 50%, when the ICC is 3% (or less than 33% when the ICC is 6%).

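### The stated random effects include no service-level time effect, so a group-by-time test would leave out service-to-service variation in change and its type I error is not secured

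*Protocol article*

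**What the plan says.** All references are to the protocol article.

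- **Analysis of primary and secondary outcome measures** sets up assessments within persons within services and states: "Random intercepts will be assumed, while allowing for the clustered nature of the data, and adjusting for appropriate covariates as fixed effects". The next sentence enters group as a fixed effect at level 3 and an integer time variable (1, 2, 3) as random at level 1. It does not say over which unit, person or service, the time effect varies.
- **Modelling strategy** says "We will treat services and individuals as random effects", the former for correlation within clusters and the latter for correlation within persons over time.
- **Trial outcomes** expects more change from Time 1 to Time 2 in the intervention group, and the analysis section likewise compares the groups on change. No group-by-time term is written out for the main effect. Such terms appear only for moderators.
- **Baseline analysis (time 1)** undertakes to account for clustering in every comparison, "to ensure correct confidence intervals and type I error rates are calculated". It also fixes the test: "All statistical tests and confidence intervals will be two-sided", and the "statistical significance level set will be at the 5% level".

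**The concern.** A service intercept describes how far a service sits above or below average at every wave. It says nothing about whether some services improve more than others. The treatment effect here is a difference in improvement, so clustering matters through the variation between services in change.

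Such variation is likely. Under Intervention, each service's own practice coaches lead the 10-week schedule, and the Discussion concedes that some staff may not give it the required time. If this variation exists and the model has no term for it, persons are treated as independent for the key contrast. Standard errors are then too small and false positives too frequent. Both primary outcomes, educator confidence and skills and parent satisfaction, would be affected.

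**Working it through.** **Inputs from the article.** "One hundred eighteen educators and 302 parents recruited from 19 participating ECEC services" gives 302/19 = 15.9 parents and 118/19 = 6.2 educators per service. Randomisation yields eight pairs plus one group of three rural services, so 2 × 8 + 1 = 17 randomised units. The ICCs of 3% and 6% come from Power analysis, where the true value is said to be unknown. They are not presented as ICCs of change.

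**The plan's own figures.** The article gives no type I error for this test. Its Power analysis states: "The required effective sample size to detect a moderate effect size (d = 0.5) with 5% significance and 80% power is 102". A t-based calculation gives 102 with a one-sided 5% test; two-sided it gives 126 (normal) or 128 (t). That mismatch is a separate matter. The attrition limits follow from 1 − 102 × DE/302, with design effect DE = 1 + (m − 1) × ICC. With 17 units (m = 17.8) they are 49.2% and 32.3%, close to the stated 50% and 33%. With 19 services they are 51.1% and 36.0%.

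**Why the intercepts cancel.** For person i in service j at time t, take

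Y_ijt = b0 + b1·G_j + b2·t + b3·G_j·t + u_j + v_ij + e_ijt.

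Then Y_ij2 − Y_ij1 = b2 + b3·G_j + (e_ij2 − e_ij1). The service effect u_j and the person effect v_ij are gone. On one simulated dataset, the three-level random-intercept fit and ordinary regression on change scores gave the same estimate (−0.3143) and the same standard error (0.1199).

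A person-level slope adds variance to each person's change, but no covariance between persons in the same service. Only a term such as w_jt, varying by service and time, adds (w_j2 − w_j1), which everyone in a service shares.

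**Size if the ICC of change is 3% or 6% (assumption).** The omitted variance understates the standard error by √DE, and true type I error = 2 × [1 − Φ(1.96/√DE)].

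| Group | m | DE (3% / 6%) | True error (3% / 6%) |
|---|---|---|---|
| Parents, all | 15.9 | 1.447 / 1.894 | 10.3% / 15.4% |
| Parents, 33% lost | 10.6 | 1.289 / 1.578 | 8.4% / 11.9% |
| Parents, 50% lost | 7.9 | 1.208 / 1.417 | 7.5% / 10.0% |
| Educators, all | 6.2 | 1.156 / 1.313 | 6.8% / 8.7% |

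Example: for parents at 3%, DE = 1 + 14.9 × 0.03 = 1.447, 1.96/√1.447 = 1.63, and the two-sided tail is 10.3%.

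**Size by simulation.** Here 3% and 6% are cross-sectional ICCs. Assumed: 50% to 100% of the service variance is stable over time, and person-level autocorrelation is 0.5 or 0.7. There were 19 services, complete data at three waves, no true effect, 4,000 runs per setting, and a Wald test of group-by-linear-time in a random-intercept model.

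| Service variance that is stable | Parents | Educators |
|---|---|---|
| 100% | 4.6–5.6% | 5.2–5.4% |
| 90% | 6.2–8.1% | 5.0–6.4% |
| 80% | 7.7–12.7% | 5.7–7.7% |
| 50% | 10.9–20.4% | 7.1–11.3% |

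Adding a person-level random slope changed these rates by only about 0.3 percentage points. A t-test on service-level slopes stayed at 4.4–5.6% in every setting.

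**The case against.** The strongest reply is that the article does not describe a model with random intercepts and nothing else. It also makes time random. If that effect varies between services, the problem largely disappears. This stands: a reader might infer that the plan uses intercepts only and ignores clustering, and the text supports neither. But the article places time at level 1 and names no service-level time effect, so the reading that would rescue the plan is not the one it states.

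Second, the group-by-time test is inferred. If the reported effect were the plain group coefficient, the service intercept would enter its standard error. This is also true, but such a coefficient would not be the difference in change that Trial outcomes sets as the expectation.

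Third, the size cannot be read off the documents. A reader might conclude that type I error is at least doubled. That requires an ICC of change of about 3% or more with about 16 parents per service. The article gives no such ICC, inflation is nil when service effects are stable, and it is modest for educators in most settings tried. The exact match with a change-score regression is likewise a simple-case result. With three waves, covariates, dropout or binary outcomes it need not be exact.

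Finally, estimation method and degrees of freedom are commonly left to a full analysis plan. Agreed, and their absence is not the complaint. The complaint is about the random-effects structure that the article does state.

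**Conclusion.** The point holds in conditional form. As written, the model has service and person intercepts and a level-1 random time effect, and no term for services differing in change. If the contrast is group-by-time, correct type I error depends on an unstated assumption that services do not differ in change.

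The mechanism is certain for the model as stated. The size rests on assumptions: nominal error if service effects are fully stable; about 10% or 15% for parents and 7% or 9% for educators if the ICC of change is 3% or 6%; and lower figures after attrition. A general claim of doubled error, or that clustering is ignored altogether, goes beyond the documents.

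**What to change.** 1. Write out the primary contrast as the group difference in change from Time 1 to Time 2. By Time 3 the control group has also received the intervention (Data collection timepoints).
2. Reconcile the two adjacent sentences on random effects and say over which unit time varies.
3. Add a service-by-time random effect. Alternatively, analyse Time 2 with Time 1 as covariate and a service random intercept, which then captures variation between services in the adjusted outcome.
4. Use small-sample degrees of freedom suited to 17 to 19 units, for example REML with Kenward-Roger (about 17 − 2 = 15), and report a service-level t-test or permutation test as a check.

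The cost is a change of wording and somewhat wider intervals. Trial status describes Time 2 data as still being collated, and Data Availability says nothing had been analysed, so at the time of writing the change could still precede the analysis.
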